## 8. Methodology notes

### A. WASH IN, REGIMEN AND OBSERVATION PERIODS

Delivery of two 15 minute nebulisers with a 5 minute gap with a 2.5mg salbutamol dose were selected to represent real-life nebuliser delivery in the acute setting. Titration of oxygen before and during the regimens represents recommended evidence based on best practice.

Maintenance of any nasal cannulae oxygen therapy at a constant flow during the observation period is designed to assess the risk of rebound hypoxia (a reduction in SpO2 following abrupt cessation of oxygen therapy to below the baseline level prior to instituting oxygen therapy). To detect any rebound hypoxemia a constant fraction of inspired oxygen is required. The results would represent the risk of rebound hypoxia in the situation that oxygen saturation monitoring does not occur following the abrupt cessation of high concentration oxygen therapy.

### B. PRIMARY OUTCOME

Elevated pCO2, is a potentially harmful physiological response to oxygen administration and predictor of adverse clinical outcome. This allows a

robust power calculation and direct comparison to previous case and interventional studies that have investigated the use of oxygen driven nebulisers.

### **C. CLINICALLY SIGNIFICANT OUTCOMES**

A rise in  $PtCO_2$  from baseline of  $\geq 4$  mmHg is considered a physiologically significant change and  $\geq 8$  mmHg a clinically significant change, based on previous definitions. A change in pH  $\geq 0.06$  is based on the magnitude of the difference in pH that is expected to result from an increase in  $PaCO_2$  and  $\geq 8$  mmHg and has clinical relevance as a marker of requirement for NIV in an exacerbation of COPD.

### **D. CAPILLARY BLOOD GAS SAMPLING**

CBG allows accurate measurement of  $pCO_2$  and pH, and is a less invasive alternative to ABG measurement. Whilst the earlobe is the preferred site for  $pO_2$  measurements, sampling blood from the fingertip or earlobe accurately reflects arterial  $pCO_2$  and pH over a wide range of values. Fingertip sampling by retractable lancets as used commonly for blood sugar measurements is more familiar to participants and tends to yield better blood flow than earlobes. pH is a valuable outcome measure as it is an independent predictor of death in exacerbations of COPD. Fingertips will be used in the first instance. However, in the event of unsuccessful sampling from a fingertip (e.g. sample too small) or contraindication (e.g. if a participant has particularly thick/tough skin on examination), then the earlobe can be used as a back-up site.

### **E. TRANSCUTANEOUS MONITORING**

The transcutaneous monitor provides continuous and non-invasive  $PtCO_2$  monitoring. The accuracy of  $PtCO_2$  monitoring has been shown in a variety of settings including in healthy subjects, acute exacerbations of COPD, sleep disorders, critical illness, and other patients.

---

## **9. Safety Monitoring**

There will be a Data Monitoring Safety Board comprising independent physicians, which will review data from any participants in which an SAE or rise in  $PtCO_2$  of

$\geq 10$  mmHg occurred. This meeting will occur after 50% of participants have been recruited, or will be arranged sooner if 5 patients experience a  $P_tCO_2$  rise of  $\geq 10$  mmHg. The meeting will also be brought forward should any investigator have safety concerns – such as several patients in succession experiencing  $P_tCO_2$  elevation, but not meeting the number of 5. This meeting will include experts independent from the study.

---

## **10. Power and Statistical Methods**

A difference in  $PaCO_2$  of 4 mmHg represents a physiologically significant change.  
 In our controlled study of oxygen versus air driven nebulisers in stable COPD the standard deviation of  $P_tCO_2$  was 5.5. With 90% power and alpha of 5% this requires a total of 82 patients to detect a 4 mmHg difference. We anticipate a drop-out rate of <10% so our target recruitment is 90 patients. Analysis will be by intention to treat. Participants recruited will be stratified in to groups that were receiving oxygen immediately prior to randomisation or those that were not. Our primary analysis is ANCOVA with  $P_tCO_2$  as the response variable, and randomised treatment and baseline  $P_tCO_2$  as co-variables. For other continuous outcome variables we will also use similar ANCOVA. Exploratory analyses for  $P_tCO_2$ , heart rate and  $SpO_2$  taken at five minute intervals will be presented graphically and analysed by mixed linear models.

---

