## 4. Randomisation and blinding

### A. RANDOMISATION

Randomisation will be 1:1 via a block randomised (block size 6) computer generated sequence, provided by the study statistician independent of recruitment and assessment of participants. The allocated intervention will be stored in an opaque sealed envelope and opened at the time of randomisation by the un-blinded investigator.

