## **E. RANDOMISED REGIMEN**

### **i. Baseline measures**

- a. At the end of the wash in and immediately prior to the randomised regimen the un-blinded investigator will take a CBG, as per the SOP. On visualisation of blood entering the capillary tube they will ask the blinded investigator to record the time and PtCO2.

- b. Immediately after the CBG sampling, the following baseline (t=0 min) measurements will be made:
  - i. The un-blinded investigator will record the time, SpO2 and nasal cannulae oxygen therapy flow (if any).
  - ii. The blinded investigator will record the time, PtCO2 and heart rate

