## **ii. Randomisation**

The randomisation envelope will be opened by the un-blinded investigator and regimens applied as below.

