### C. PRIMARY OUTCOME VARIABLE

- i.  $P_t\text{CO}_2$  at completion of the second nebulisation (at  $t=35\text{min}^*$ ), adjusted for baseline.

\*or the last recorded measurement should the  $t=35$  measurement not be obtained (e.g. study terminated early due to rise in  $P_t\text{CO}_2 \geq 10\text{mmHg}$ ).

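### Section 10 says participants are stratified by oxygen use before randomisation, but neither the described allocation nor the primary ANCOVA uses that factor

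*Protocol*

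**What the plan says.** Section 10 (Power and Statistical Methods) says: "Participants recruited will be stratified in to groups that were receiving oxygen immediately prior to randomisation or those that were not". The next sentence sets the primary analysis as an ANCOVA on PtCO2 with "randomised treatment and baseline $P_tCO_2$ as co-variables". Other continuous outcomes get a similar ANCOVA. No subgroup, interaction or by-stratum analysis on oxygen use appears anywhere in the protocol.

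Section 4.A gives the allocation method: "Randomisation will be 1:1 via a block randomised (block size 6) computer generated sequence". On concealment it adds: "The allocated intervention will be stored in an opaque sealed envelope and opened at the time of randomisation by the un-blinded investigator". At the study visit, section 6.E.ii says only: "The randomisation envelope will be opened by the un-blinded investigator and regimens applied as below". Neither place mentions strata, separate lists, or choosing an envelope by oxygen status.

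Section 6.E.i has the un-blinded investigator record any nasal cannula oxygen flow at t=0, before the envelope is opened. The factor is therefore known in time both for stratified allocation and for adjustment.

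**The concern.** A declared stratification factor normally shows up in two places: in how the list is built and in the analysis model. Here it shows up in neither. The statistician preparing the sequence cannot tell from the protocol whether to make one list or two, and no later analysis document can change how the envelopes were filled.

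What is at stake depends on what was meant:

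- **Randomisation stratified, stratum omitted from the model.** Stratification removes between-stratum variation from the treatment contrast, but the model leaves that variation in its residual. The reported standard error is then larger than the true one. Intervals are too wide and some power is given away.
- **Randomisation not stratified.** The balance that section 10 implies is not secured, and the model does not correct for an imbalance that arises.
- **Grouping for analysis only.** No analysis that uses the groups is stated.

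**Working it through.** **1. The plan's own figure.** Inputs from section 10: difference 4 mmHg, SD 5.5, power 90%, alpha 5% (taken as two-sided). The normal approximation gives n per arm = 2 × 5.5² × (1.960 + 1.282)² / 4² = 60.5 × 10.51 / 16 = 39.7, so 40 per arm and 80 in total. The t-test gives power 0.895 at 40 per arm and 0.902 at 41, so 82 in total. The stated 82 reproduces. It uses no stratum term, so nothing below changes it.

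**2. Stratified allocation, stratum omitted.** Assumptions not in the protocol: half of participants on oxygen; stratum effect g on PtCO2 at t=35 given baseline PtCO2; total residual SD 5.5 including the stratum; N = 82.

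- Within-stratum SD: e = √(5.5² − g²/4)
- SE reported by the model without the stratum ≈ 5.5 × √(4/82) = 1.215
- True SE ≈ e × √(4/82)
- Actual type I error ≈ 2 × [1 − Φ(1.96 × 5.5/e)]
- Power, omitted ≈ Φ(4/true SE − 1.96 × 5.5/e)
- Power, included ≈ Φ(4/true SE − 1.96)

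With the numbers in:

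| g (mmHg) | e | True SE | Type I error | Power omitted | Power included |
|---|---|---|---|---|---|
| 0 | 5.500 | 1.215 | 0.050 | 0.909 | 0.909 |
| 2 | 5.408 | 1.194 | 0.046 | 0.912 | 0.918 |
| 4 | 5.123 | 1.132 | 0.035 | 0.924 | 0.942 |
| 6 | 4.610 | 1.018 | 0.019 | 0.944 | 0.976 |

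Simulation under the same assumptions (4,000 runs per case, blocks of 6 within stratum) agrees:

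| g (mmHg) | Type I error, omitted | Type I error, included | Power omitted | Power included | Loss (points) |
|---|---|---|---|---|---|
| 0 | 0.050 | 0.049 | 0.899 | 0.897 | none |
| 2 | 0.048 | 0.051 | 0.899 | 0.904 | 0.5 |
| 4 | 0.034 | 0.045 | 0.915 | 0.933 | 1.8 |
| 6 | 0.018 | 0.051 | 0.936 | 0.972 | 3.6 |

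**3. One unstratified sequence.** In the same simulation, type I error is about 0.05 with or without the stratum term (range 0.046 to 0.054). Adjusting raises power from 0.899 to 0.935 at g = 4 and from 0.900 to 0.972 at g = 6. It makes little difference at g = 0 (0.900 and 0.895) or g = 2 (0.904 and 0.908).

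The arms differ by 3.7 oxygen users on average (95th percentile 9), against 0.8 (95th percentile 2) when stratified. With about 41 per arm, a difference of 9 is 9/41 = 22 points. At g = 4 that moves the estimate, in that particular trial, by 0.22 × 4 ≈ 0.9 mmHg. The average difference moves it by 3.7/41 × 4 ≈ 0.4 mmHg.

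With 90 participants, 45 on oxygen and 45 per arm, the hypergeometric probability of an imbalance of at least 10 points is 0.399, and of at least 20 points 0.091.

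**The case against.** The strongest reply is that nothing here is a contradiction. Section 4.A is silent on strata; it never says the list is unstratified, and blocks of 6 could be generated within each oxygen group. The sentence in section 10 sits among the analysis methods and does not say that randomisation is stratified, so it may mean grouping for description or subgroups. This stands as far as it goes. The mismatch is between an explicit statement and an omission, and a reader who concludes that the two sections cannot both be followed goes further than the text allows. It does not remove the point, because on each reading the protocol gives the factor no use.

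A reader might also infer that the primary result is biased or its error rate inflated. The calculations show neither. Omitting the stratum after stratified allocation errs on the conservative side. Under an unstratified list, chance imbalance is already allowed for in the standard error.

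Nor does the protocol call oxygen use prognostic. Sections 6.E.iii and 6.F handle nasal oxygen differently by arm for participants already using it. That suggests, if anything, a treatment effect that differs by oxygen use, which a main-effect term would not address. The sizes above rest on assumed stratum effects. The larger ones equal or exceed the 4 mmHg difference sought, and even then simulated power with the stratum omitted stays at about 0.90 or higher.

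Finally, a separate analysis plan may add the term. But this protocol names the primary model's covariates outright, so the mismatch is in the document as it stands.

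**Conclusion.** The point holds as an inconsistency that should be fixed. Section 10 declares stratification by pre-randomisation oxygen use, and neither the described allocation nor the stated ANCOVA carries it.

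- **If randomisation is stratified:** the estimate is unbiased and the test conservative. For assumed stratum effects of 4 to 6 mmHg, type I error is roughly 0.02 to 0.03 and the power loss about 2 to 4 points. At 0 to 2 mmHg the consequence is negligible.
- **If it is not stratified:** the test is valid, balance on oxygen use is not secured, and a prognostic factor of that size would be worth adjusting for.

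These figures assume half the participants on oxygen, a total residual SD of 5.5 mmHg and 82 analysed. The protocol gives neither the share on oxygen nor the stratum effect. The documents do not support a claim of bias, of inflated type I error or of an underpowered trial.

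**What to change.** 1. In section 10, add oxygen status at t=0 (on nasal oxygen or not) as a factor in the primary ANCOVA and in the similar secondary ANCOVAs. This calibrates the standard error if allocation is stratified. If it is not, it adjusts for chance imbalance.
2. Make sections 4.A and 10 agree. Either describe in 4.A a separate block-of-6 sequence and envelope set for each oxygen stratum, and say in 6.E.ii that the envelope comes from the set matching the t=0 status; or reword section 10 to say that the grouping is for analysis only, and name that analysis.

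The cost is one model degree of freedom and, if allocation is stratified, a second set of envelopes prepared before recruitment. No extra participants or measurements are needed, and the 82 and 90 stand.

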## **11. Note on changes to protocol since previous version**

This is Version 2.0, which was not submitted in the initial application of ethics approval.

---

